### Randomization and blinding

The patients who volunteer to take part in the study will be randomly allocated into two groups (the experimental and control groups), using a computational random number generator (EPIDAT 3.1, Xunta de Galicia) with randomization codes created by [name]. This will assign patients to a combined functional apraxia rehabilitation group or a control group with an allocation ratio (1:1). During the randomization process, patients will be blinded to their treatment allocation. The neurologist will examine the patients for eligibility criteria and collect all the baseline demographic variables but will not be involved in the rest of the study or preparation of the randomization codes. Treatment allocation will be concealed and patients and study personnel will be blinded to the treatment assignments until after the database has been locked. During the trial, all the outcome measures will be collected by three therapists, who will be blinded to the group allocation. Treatment interventions will all be carried out by an occupational therapist with wide clinical experience, who will be blinded to the outcome measures and baseline examination findings but not to the patients’ treatment allocation, although this allocation will not be revealed to the therapists who gather the outcome measure data. Criteria for receiving discontinued intervention will be as follows: 1) the participant requests voluntarily to miss any session, or 2) the interventions produce a significant improvement or worsening of apraxia disease. As part of the strategy to improve adherence to intervention, patients will be informed about the relevance of the treatment in each session, and they will be telephoned weekly to remind the date of the sessions. The final result of the study will be reported to the patients in both groups.

### Combined functional rehabilitation approach to apraxia (experimental group)

The functional rehabilitation approach for upper limb apraxia consists of occupational therapy intervention based on two complementary approaches. Information about these approaches has been published separately, and there is evidence that both approaches are effective [6, 10, 26]. The experimental group will receive an 8-week combined functional rehabilitation program at home with an occupational therapist on 3 days per week in 30-min intervention periods, focusing on restorative and compensatory techniques for upper limb apraxia. Once the occupational therapist has identified the patient’s needs, the restorative program will be used in the first two of the weekly sessions, and the compensatory methods in the last session of the week. Both methods will be used to improve the patients’ functional performance, allowing them to be more independent in different daily living contexts, especially in the home.

In the restorative approach, developed by Smania et al. [6, 10], treatment is designed in three sections, directed towards transitive, intransitive-symbolic and intransitive-nonsymbolic gestures, respectively. Transitive gesture training is subdivided into three phases: A, B, and C. In phase A, the patient is required to demonstrate the use of common tools. In phase B, the patient is shown a picture illustrating a transitive gesture and is then required to mime or imitate that gesture. In phase C, the patient is presented with a picture showing a common tool and is then asked to demonstrate how it is used by pantomiming. Each phase contains 20 items. When the patient is able to correctly perform at least 17 of the 20 items, that phase is concluded and the following phase is initiated [6, 10].

Intransitive-symbolic gesture training is also subdivided into phases A, B, and C, depending on the number of contextual cues used under the different conditions. In intransitive-nonsymbolic gesture training, the patient is asked to imitate meaningless intransitive gestures previously shown by the examiner. Twelve gestures, involving six proximal and six distal joints, are delivered. Half of the gestures are static, and the rest are dynamic. Patients who are unable to perform the gesture properly are assisted by the examiner with verbal or other appropriate facilitation [6, 10].

The compensatory approach is based on the work of Van Heugten et al. [6, 26]. The treatment consists of therapy sessions that focus on teaching patients strategies to compensate for deficits linked to apraxia. Greater improvement in ADL functioning is typically expected from implementation of the compensatory approach, rather than the recovery of motor impairments. Patients become more independent in performing everyday activities when they are taught internal and external strategies, such as the use of oral and written instructions, or picture sequences that can compensate for any functional deficits caused by apraxia during the execution of their everyday activities. Compensation can be provided in two ways: externally (by the therapist), using materials that help the patient to perform an action (for example, photographs depicting the correct sequence of an action), and internally (generated by the patients themselves) by relying on intact cognitive functions (for example, verbalizing the sequence of distinct actions the patient is supposed to complete) [6, 26].

The decision about which activity to work on will be made collaboratively with the patient and the occupational therapist. The therapist will take into account the decision tree and principles used by Van Heugten et al. to guide the selection of a specific activity and apply a checklist of activities. The checklist will consist of an assessment of the activities the patient performed prior to the stroke and those activities that are relevant to the patient for future performance. The interventions implemented during the compensatory sessions are based on specific difficulties noted during standardized ADL observations [6, 26].

ADL activities are conceived as three successive phases, conforming to the information processing framework: initiation, execution, and control. For example, a patient with apraxia who cannot use objects appropriately may have a deficit at any one of the stages of the activity being performed. By evaluating the different components of the activity, the structure of the deficit can be recognized, and the design of the treatment can be formulated accordingly [6, 26].

### Traditional health education protocol (control group)

The control group patients will receive a health education program only. They and their caregivers will attend a series of education workshops where they will be given information about what having a stroke involves, the meaning of upper limb apraxia, the implications of upper limb apraxia on daily living at home, and the common types of challenges arising from apraxia with respect to the daily use of a person’s upper limb. The workshops will take place at the patient’s home once a month over a 2-month period. After completion of the study, this group will be offered the opportunity to participate in the combined approach intervention, although the data from this will not be used in the statistical analysis.

### Assessment

#### Primary outcome measure

##### Barthel Index

The Barthel Index (BI) for ADLs is a widely used standardized scale for assessing functional disability in basic ADLs. It scores ten basic activities: bowel control, bladder control, grooming, toilet use, feeding, transfer, mobility, dressing, using the stairs and bathing. The score generated varies from zero (totally dependent) to a maximum score of 20 (totally independent). It has good interobserver reliability, with a Kappa statistic between 0.47 and 1.00, and good intra-observer reliability, with a Kappa statistic between 0.84 and 0.97 [37]. In a study involving a poststroke participant group, the internal consistency of the BI was a Cronbach’s alpha of 0.92 [38].

### Secondary outcome measures

#### General functionality and autonomy

The Lawton and Brody Instrumental Activities of Daily Living Scale is a questionnaire used to assess the ability to develop the instrumental activities necessary for living independently in the community. It is a self-administered scale validated for the Spanish population [39]. The maximum score of 8 points indicates complete independence, a score of 6 to 7 mild dependence, 4 to 5 moderate dependence, 2 to 3 severe dependence, and 0 to 1 total dependence. It has high inter- and intra-observer coefficients of reliability (0.94) and high test-retest reliability (0.95) [39, 40].

The Observation and Scoring of ADL Activities is a test that consists of observing the performance of activities of daily living with a system of standardized observations specially developed for assessing disability caused by apraxia. The overall score varies from totally dependent (0) to fully independent (3). The Kappa statistic shows values higher than 0.70, indicating considerable agreement [38]. The inter-observer reliability of each assessed activity varies with the intraclass correlation coefficients from 0.62 to 0.98 [41].

#### Neuropsychological tests

The De Renzi Test for Ideational Apraxia assesses ideational apraxia in the upper limbs and requires the use of real objects. Patients are asked with words and gestures to take an object in their hands and demonstrate how they would use it. Two points are assigned for an immediate correct response, and one point is assigned if a correct performance is preceded by hesitation or a protracted latency period during which wrong or unsuccessful movements are presented or if the performance is conceptually correct but the actual movements are somewhat inaccurate or awkward. For any other type of error, no points are given. The score varies from zero to 14 points [16].

The De Renzi Test for Ideomotor Apraxia requires patients to reproduce a wide variety of intransitive gestures, that is, gestures that do not require the use of objects. The gestures may be symbolic (for example, the OK sign) or nonsymbolic (hand under the chin). Patients are assigned a maximum of three points if they perform the gestures correctly after the first demonstration, and two or one points, depending on whether they need a second or third demonstration. If all the demonstrations are unsatisfactory, no points are given. The test consists of 24 items and the total test score varies from zero to 72 points [42].

Recognition of Gestures tests both transitive and intransitive-symbolic gestures, following the recommendations of Smania et al. [10]. For transitive gestures, the patient is given three pictures showing an action performed a) with an object, b) with a semantically related but inappropriate object, or c) with a semantically unrelated inappropriate object. Patients are required to indicate the picture in which the correct transitive gesture is reproduced. As for intransitive symbolic gestures, the patient is given three pictures showing different symbolic gestures, one of which is related to a context represented in another picture. The remaining two pictures show gestures with or without postural affinities with the correct gesture. The patient is requested to indicate the picture showing the gesture related to the context. The test includes five transitive and five intransitive gesture recognition trials. One point is given for each correct response, with the resultant scores varying from zero to ten points [10].

The Test of Upper Limb Apraxia (TULIA) for Comprehensive Assessment of Gesture Production has a total of 48 items, grouped into six subtests, for imitating gestures and simulating gestures that are nonsymbolic (meaningless), intransitive (communicative), and transitive (related-objects). It has a Likert scale from zero to five points per item, with a total score varying from zero to 240 points [43]. Evidence shows that this test is a reliable and valid assessment of gesture production. It can therefore be easily applied for the purposes of research and clinical practice. It has a good to excellent internal consistency and test-retest reliability at both the level of the six subtests and the individual level of the items. For test-retest reliability at item level in patients examined three times within 24 hours, it has been shown that most items (*n* = 39) had a good-to-perfect degree of agreement (varying from 0.66 to 1.0) [43].

#### Overall quality of life

The Quality of Life Scale for Stroke (ECVI-38) is a self-administered questionnaire, but in cases where the patient is unable to read or understand the questions, it can be completed by a relative or the primary caregiver. It has 38 items grouped into eight subscales: physical, communication, cognition, emotions, feelings, basic activities of daily living, common activities of daily living, and social and family functioning, plus two additional questions about involvement in sexual relationships and occupational activity. Responses are categorized depending on the percentage obtained of the total maximum score of 100 points. Less than 25 % means unaffected, between 25 and 50 % indicates mild disease, between 50 and 75 % shows moderate impairment, and 75 % or more means severely affected. This test showed a test-retest reliability varying from 0.81 to 0.96, calculated with intraclass correlation coefficients examined at 1 and 2 weeks [44, 45].

##### Incidence of adverse events

Although no previous adverse effects have been reported for this intervention, participants will be asked to provide information about any potential adverse events. These will be recorded by the researcher during the trial and follow-up. Adverse events might include upper limb pain an hour after treatment, musculoskeletal impairments, and swelling or increased muscle tone in the upper limb. The researcher will collect data on these events, such as time and date of occurrence, severity, measurements related to the treatment and causal relationship with the intervention. Severe adverse events will be reported immediately to the principal investigator ([name]).

### Sample size

Based on previously published findings on the use of rehabilitation treatments by poststroke patients with upper limb apraxia [14], a clinically important difference pre-post treatment of 2.44 points on the Barthel Index for ADLs (primary outcome) was used to calculate the sample size required to detect the increase in patients’ functional ability with combined functional rehabilitation (experimental group) versus the traditional health educative protocol (control group), using the PASS 13 (Power Analysis and Sample Size) program (http://www.ncss.com/). A sample size of 15 patients per arm was estimated to provide a 95 % confidence interval (CI) with a power of 80 %, assuming a standard deviation of 3.10 points for this difference and a two-sided test (α) of 0.05. The sample size has been increased to a total of 40 to allow for a loss to follow-up of up to 22 %.

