### Limitations

The first limitation involves the methodology. If it were feasible, a three-arm study including a restorative, a compensatory and a combined intervention group might provide greater insights. However, we have designed a study for investigation purposes in which a combined intervention is compared with a control group, since we could find no previous studies that have used this intervention approach with apraxia disorders.

Since the two groups receive different amounts of intervention, there is also potential for attention bias. However, the authors are required to comply with the protocol for upper limb apraxia at the hospital from which the patients are recruited, and it is not possible to change the control group.

The second limitation is that not all the original validation articles of the measures used in the present study, such as the De Renzi test for ideomotor apraxia, the recognition of gestures tests and the Barthel test, reported test-retest reliability. This is a critical aspect when potential clinical changes over time are being measured. Despite this, we have opted to use these tools because of the frequency with which they have been utilized in previous apraxia research.

The third limitation is that we could find no previous reports that show the effect size of the combined intervention; therefore, our sample size may not be adequate. However, in a clinical context, we hope that the combined approach achieves at least the minimum clinically important difference shown for other apraxia treatments. It is for this reason that the sample size has been calculated based on this value. In addition, recruiting patients with upper limb apraxia is difficult. As a result, previous research on this issue has used a smaller or similar sample size.

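### The stated inputs do not give 80% power at 15 per arm for the between-group comparison: power is about 55% (68% with all 40 patients), and 80% needs 27 per arm

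*Protocol article*

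**What the plan says.** The Sample size section of the protocol article takes as its target "a clinically important difference pre-post treatment of 2.44 points on the Barthel Index for ADLs (primary outcome"), drawn from an earlier study of apraxia rehabilitation. It says the calculation is for detecting the gain in functional ability "with combined functional rehabilitation (experimental group) versus the traditional health educative protocol (control group"). The remaining inputs are given as "assuming a standard deviation of 3.10 points for this difference", "a two-sided test (α) of 0.05" and "with a power of 80" per cent. The result is worded as "A sample size of 15 patients per arm was estimated to provide" that power, and the number is raised to 40 in total for a loss of up to 22%. The software is named (PASS 13), but the procedure within it is not.

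The Randomization and blinding section gives 1:1 allocation. The Statistical analysis section plans a repeated-measures ANOVA for the intervention effect and the group-by-time interaction.

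The Limitations section concedes that the sample may be too small. The reason it gives is that no effect size for the combined intervention has been reported. It then says the size rests on the minimum important difference seen with other apraxia treatments: "It is for this reason that the sample size has been calculated based on this value".

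**The concern.** The comparison named is between two independent groups, yet 15 per arm is small for a standardised effect of about 0.79 in such a comparison. The target is also worded as a pre-post difference, which raises the question of whether a one-group calculation was carried over to a two-group trial.

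What is at stake is the power claim for the primary outcome. A null result would be read against a stated 20% chance of missing a true 2.44-point difference. If the claim is wrong, that chance is much higher, and the Limitations text would not tell the reader, because it locates the doubt in the unknown effect size and not in the calculation.

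**Working it through.** **Inputs (all from the Sample size section).** Difference 2.44; SD 3.10, attached in the text to that difference; two-sided alpha 0.05; power 80%; 15 per arm; loss up to 22%. Allocation is 1:1.

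**Standardised effect.** d = 2.44 / 3.10 = 0.787.

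**Step 1: try to reproduce 15 as a two-sample comparison.**
- Normal approximation: n per arm = 2 × (1.960 + 0.842)² / 0.787² ≈ 25.3, so 26.
- Exact noncentral t, with noncentrality d × √(n/2) and 2n − 2 degrees of freedom: 26 per arm gives 79.5% and 27 per arm gives 81.0%, so 27 are needed.
- A one-sided test would need 20 (normal approximation) or 21 (t) per arm. The text says two-sided in any case.

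None of these gives 15.

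**Step 2: try a one-sample or paired t-test.** Noncentrality d × √n, with n − 1 degrees of freedom.
- n = 14: noncentrality 0.787 × √14 = 2.95, power 77.7%.
- n = 15: noncentrality 0.787 × √15 = 3.05, power 80.9%.

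The smallest n reaching 80% is exactly 15.

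**Step 3: check the loss allowance.** 15 / (1 − 0.22) = 19.2, so 20 per arm and 40 in total. This step reproduces; it carries forward the base of 15.

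**Step 4: power of the two-sample t-test at the planned sizes.**

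| Evaluable per arm | Noncentrality | Power | Chance of missing 2.44 | Difference detectable with 80% power |
|---|---|---|---|---|
| 15 | 0.787 × √7.5 = 2.16 | 54.8% | 45.2% | 3.29 |
| 20 (no loss) | 0.787 × √10 = 2.49 | 67.9% | 32.1% | 2.82 |

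The normal approximation gives 57.8% and 70.2%, so the choice of method does not alter the conclusion. With the full 22% loss, 40 × 0.78 = 31.2 patients remain, or 15 to 16 per arm, where power is 54.8% to 57.7%.

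**Step 5: what would have to be true for 15 per arm to give 80%.** With the difference held at 2.44, the SD entering the two-sample test would have to be about 2.30, not 3.10.

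**Relation to the planned analysis.** With two time points, the group-by-time test in a repeated-measures ANOVA is the two-sample t-test on the change scores. If 3.10 is the SD of the pre-post change, as the text indicates, Step 4 is therefore the matching calculation for baseline to 8 weeks, and the benefit of pairing is already inside the 3.10.

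**The case against.** The strongest reply is that 15 can be reached by other routes.
- If 3.10 were the SD of a single score, a two-sample comparison at 15 per arm would have 80% power with a pre-post correlation of about 0.67 (baseline-adjusted analysis, SD 3.10 × √(1 − 0.67²) = 2.30) or 0.725 (change score, SD 3.10 × √(2 × 0.275) = 2.30).
- If 3.10 were the SD of a difference between two independent patients, the per-arm SD would be 3.10 / √2 = 2.19 and 14 per arm would suffice.
- Sample-size routines for repeated measures commonly ask for a correlation, and the planned analysis is of that type.

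What stands is that the origin of the 15 is not proven. A reader might infer from the exact match that a paired formula was certainly applied to each arm. The article names the software but not the procedure, so the match is strong evidence and no more. What does not stand is the rescue: no correlation is stated, and the text ties 3.10 to the pre-post difference.

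A reader might also infer that true power is lower still, because controls may improve and the Discussion calls spontaneous recovery of apraxia common. The documents do not support this. The same sentence of the Discussion goes on to say, in awkward wording, that such recovery typically does not extend to daily-living ability, which is the domain of the primary outcome. Whether 2.44 was a within-group change or a between-group difference in the cited study cannot be checked here, and the Sample size section can be read as targeting a between-group difference in change.

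Finally, the Limitations section already warns that the size may be inadequate. That softens the 80% claim but does not correct it: the stated reason is a different one, and the text then defends the number as resting on the important difference.

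**Conclusion.** The point holds as an error of stated power. For the comparison the section names, its own inputs give about 55% power at 15 per arm and 68% at 20 per arm, against a claimed 80%. The required size is 27 per arm, which is 1.8 times the stated 15. The chance of missing a true 2.44-point difference is 32% to 45%, not 20%.

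This rests on three assumptions: 2.44 is the between-group difference to be detected, 3.10 is the SD of the pre-post change in each arm, and no further variance reduction applies. The first two follow the wording of the section; the third follows from its silence. The conclusion does not depend on how the 15 was obtained, nor on any assumption about change in the control arm.

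**What to change.** Reword two places in the protocol article.

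1. **Sample size.** State that for a between-group difference of 2.44 points in Barthel change (SD 3.10, two-sided alpha 0.05), 15 evaluable patients per arm give about 55% power and 20 per arm give about 68%. Add that the differences detectable with 80% power are 3.29 and 2.82 points respectively. If a correlation or another procedure was in fact used, state it with its value, so that the 15 can be reproduced.
2. **Limitations.** Say that the size falls short of 80% power even if the 2.44-point difference is true, separately from the uncertainty about the effect of the combined intervention.

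The cost is a few sentences and a less favourable power statement. Enrolment, design and primary analysis stay as they are, which suits the article's own remark that these patients are hard to recruit.
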